### **8.2 Sample Collection:**

**8.2.1** BAL research samples will be collected throughout the project at time points and quantities described here.

**At Bronchoscopies:**

- g) As part of routine post-transplant management lung transplant recipients attend for surveillance bronchoscopy at 1 day, 2 and 6 weeks and 3, 6, 9, 12 and 18 months post-transplant, at which point BAL samples are collected.
- h) On occasions of clinical concern, additional bronchoscopies may be scheduled as part of patient care. At these clinical relevant bronchoscopies, BAL samples are also collected.

30mls of BAL will also be collected from both the transplanted lung and the native lung of participants who receive a single lung transplant

**8.3 Participant Involvement:**

All participants will be followed for a total of 3 years following lung transplant.

Lung transplant recipients enrolled in the study would not need to make any additional trips to the Alfred hospital nor undertake any additional investigations. Collection of research related samples at bronchoscopies will coincide with routine biopsy, blood and BAL collections and will not require additional procedures for the participants.

**8.4 Sample Processing:**

At bronchoscopy, blood and BAL samples will be collected from the transplanted lung according to standard clinical protocols and forwarded to microbiology for routine diagnostic assessments. These microbiological results will be analysed as an outcome variable in the current study.

Remaining BAL samples from both lungs will be processed and centrifuged at the Alfred hospital to BAL supernatant samples for biomarker analysis. These samples will then be transported to our collaborators for analysis.

**42. INCLUSION/EXCLUSION CRITERIA**

Approximately 150 patients, including 10-15 single lung transplant recipients, will be enrolled at The Alfred Hospital

Inclusion Criteria

- Adults  $\geq 18$  years of age
- Lung Transplant Recipients
- Provide Written Consent

#### Exclusion Criteria

- Long Term Follow-Up not planned for The Alfred Hospital

### 43. ANALYSIS:

Descriptive statistics will be used to determine the baseline and clinical characteristics of the subjects in the study. Univariate analysis of the biomarkers and their association with the clinical end-points of acute rejection and CLAD will be performed using the Chi-square test for equal proportion, Student's t test for normally distributed continuous variables and the Mann-Whitney U test for non-normally distributed variables. Time to acute rejection and CLAD will be analyzed using univariate and multivariate Cox proportional hazards regression, adjusting for potential confounding factors and reported using the Kaplan Meier curves. All analysis will be performed using SAS version 9.2 (SAS Institute Inc., Cary, NC, USA). A two-sided p-value of 0.05 will be considered to be statistically significant.

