## **37. BROAD PROJECT AIMS**

4.1. To establish the immune response in the serum and bronchoalveolar lavage (BAL) as measured cross-sectionally and longitudinally during the three year post-LTx and the association with later episodes of acute rejection or the subsequent development of CLAD.

4.2. To determine whether episodes of viral, fungal or bacterial infection in the LTx recipient trigger further increases in the secretion of these biomarkers and thus act as an inflammatory stimulus.

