### **5.3 Acute Rejection**

Despite the use of maintenance immunosuppression, acute cellular rejection is a common problem post lung transplant with 34% of adult LTx recipients experiencing at least one episode during the first year

post-transplant. The lung allograft is particularly susceptible to alloreactivity with the incidence of acute rejection being higher following LTx compared to other solid organ transplants. Whilst the direct effects of acute rejection are usually controlled and reversed following high-dose intravenous steroid treatment, the indirect effects remain problematic, with episodes of acute rejection being strongly associated with the later development of chronic lung allograft dysfunction (CLAD). Given the need for invasive transbronchial biopsies to provide a histological diagnosis of acute cellular rejection, we have previously evaluated biomarkers in the blood and BAL and their association with acute rejection (2-5). Functional assays of T cell and B cell function in the blood may identify patients at higher risk of acute cellular rejection. Analysis of the BAL is very useful in providing mechanistic insights into the immunology of graft function and rejection following LTx. However, BAL findings seen in acute rejection must be interpreted in the context of those described in stable lung transplant recipients, and after taking into account the confounding nature of chronic airway infection.

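### The cross-sectional acute-rejection analysis has no defined comparator and no allowance for concurrent infection, although the protocol's own background section requires both

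*Supplement*

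**What the plan says.** All references are to protocol version 4.0; no separate SAP is in the supplement.

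- Background 5.3 sets two conditions for interpretation. The first concerns the comparator: "BAL findings seen in acute rejection must be interpreted in the context of those described in stable lung transplant recipients". The second concerns infection, since the same findings are to be read only "after taking into account the confounding nature of chronic airway infection".
- Aim 4.2 (section 37) asks whether episodes of "infection in the LTx recipient trigger further increases in the secretion of these biomarkers". Infection is therefore treated as a possible driver of the same markers.
- Section 8.2 samples lavage at surveillance visits and also at clinically triggered ones: "On occasions of clinical concern, additional bronchoscopies may be scheduled as part of patient care".
- Section 8.4 describes the routine microbiology results as an outcome variable. It gives them no role as a covariate.
- Section 43 states its plan as follows: "Univariate analysis of the biomarkers and their association with the clinical end-points of acute rejection and CLAD will be performed". Three tests are named for this purpose: "Chi-square test for equal proportion, Student's t test for normally distributed continuous variables and the Mann-Whitney U test for non-normally distributed variables". Event times for rejection and for CLAD go into "univariate and multivariate Cox proportional hazards regression, adjusting for potential confounding factors". The threshold is given as: "A two-sided p-value of 0.05 will be considered to be statistically significant".

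Section 43 does not define a stable group, the unit of analysis (patient or sample), the handling of infected or clinically triggered samples, or the list of confounders.

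**The concern.** The background states how rejection lavage must be read, and the analysis section does not carry this out. A marker compared by rejection yes/no, with nothing held constant, mixes three questions: whether it separates rejection from stability, whether it separates rejection from infection, and whether infection is more or less common among patients with rejection. Only the first two are of interest.

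Three errors are possible, and which one occurs depends on how infection is distributed. If infection raises the marker and is commoner among comparators, a real rejection signal shrinks. If it is commoner among patients with rejection, the signal is overstated. If the marker responds only to infection and the shares differ, it can be reported as a rejection marker. A reader of the results could not tell which had happened. An undefined comparator also leaves the choice open until the data have been seen.

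**Working it through.** The plan states no power, effect size, SD or infection rate, so there is no figure to reproduce. The calculation below only illustrates size.

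**Inputs from the documents.** About 150 patients (section 42); 34% with at least one acute rejection in the first year (5.3); two-sided 0.05 (section 43). 0.34 × 150 = 51 with rejection, leaving 99 without.

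**Assumptions, not in the documents.** One value per patient; marker SD 1; rejection shifts the marker by d; infection shifts it by g·d; share q of the rejection group and share p of the comparators are infected.

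**Expected difference with additive effects:** Δ = d + g·d·(q − p). Each group's variance is 1 + share × (1 − share) × (infection shift)². Power = Φ(Δ/SE − 1.96) + Φ(−Δ/SE − 1.96).

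**1. Dilution.** Take d = 0.6 and let infection add nothing in the rejection group (equivalent to q = 0).
- No infected comparators: SE = √(1/51 + 1/99) = 0.172; 0.6/0.172 = 3.48; power 0.94 (simulated t-tests: 0.93).
- p = 30%, g = 1: Δ = 0.6 × 0.7 = 0.42; comparator variance 1 + 0.21 × 0.36 = 1.076; SE = √(1/51 + 1.076/99) = 0.175; ratio 2.41; power 0.67 (simulated: 0.66).

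| Infected comparators | All 99, g = 1 | All 99, g = 0.5 | Stable only (n left) |
|---|---|---|---|
| 20% | 0.79 | 0.88 | 0.92 (79) |
| 30% | 0.67 | 0.84 | 0.90 (69) |
| 40% | 0.54 | 0.79 | 0.88 (59) |

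The table uses the normal approximation; simulated values are up to about 0.03 lower. At d = 0.5 the pattern is the same: 0.83 with no infected comparators, 0.52 at p = 30% and g = 1, and 0.77 with a stable-only comparator.

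**2. The direction depends on q and p.** With g = 1:
- q = 50%, p = 30%: Δ = d(1 + 0.5 − 0.3) = 1.2d, so the contrast is inflated.
- q = p: Δ = d, so there is no bias.
- q = 20%, p = 40%: Δ = d(1 + 0.2 − 0.4) = 0.8d, so it is diluted.

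**3. A marker driven only by infection** (no rejection effect, infection shift e): Δ = e(q − p).
- e = 1, q = 50%, p = 30%: Δ = 0.20; SE = √(1.25/51 + 1.21/99) = 0.192; ratio 1.04; probability of significance 18%.
- The same shares with e = 0.5: 8.7%.
- q = 60%, p = 30%: 13.5% (e = 0.5) to 35% (e = 1).
- q = p = 30%: 5.0%.
- q = 20%, p = 40%: 8.8% to 19%, with the opposite sign.

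**The case against.** A reader might infer that the plan uses every non-rejection patient or sample as comparator. Section 43 does not say so. It leaves the comparator undefined, and all non-rejection is only the default reading of a yes/no association.

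A reader might also infer that infection is never adjusted for. The multivariate Cox model adjusts for potential confounders, and 5.3 itself names airway infection as confounding, so it is the obvious candidate. The protocol also studies infection directly in aim 4.2, in background 5.4 and in Specific Aim 5. This stands as a partial answer. The Cox model names no factor, addresses time to event rather than the state of the lung at rejection, and does not reach the univariate tests.

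The hypothesis and aim 4.1 concern prediction of later episodes. For that purpose everyone still at risk, infected or not, is a proper comparator. This stands for the Cox analysis. The protocol also plans cross-sectional analysis, and the condition in 5.3 bears on that part.

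Rejection against clean stable recipients is an extreme-group contrast and can overstate how well a marker performs in practice. This stands too, and is why that contrast should not replace rejection against all others.

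Finally, the power losses rest on assumptions. They halve or better when infection has half the effect of rejection, and they vanish when infection is equally common in both groups and effects add. This is correct.

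**Conclusion.** The inconsistency between 5.3 and section 43 is real and lies within the current version. As written, the cross-sectional analysis would give a result that the protocol's own background calls confounded. The comparator is undefined, infection is not named as a covariate, and the tests chosen could not take one.

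The documents do not support saying that rejection markers will be diluted. Dilution needs infection to move the marker in the same direction as rejection, and to be rarer, or to add less, in the rejection group. False rejection markers need infection to be commoner in that group. Under the assumptions above, power falls from 0.93 to 0.66 with 30% infected comparators and an infection effect equal to rejection's, and the false-positive rate is 18% at 50% v 30% infected with a 1 SD infection effect. Other plausible inputs give no loss, or inflation. The point merits correction because the result cannot be interpreted without the missing definitions. It does not invalidate the cohort.

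**What to change.** In section 43:

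1. For samples with both biopsy and microbiology results from the same bronchoscopy, classify each as rejection only, infection only, both, or stable (surveillance visit, neither). State how samples without a biopsy are handled, since v4.0 does not say that biopsy is done at every listed visit.
2. Replace the unadjusted tests for acute rejection with a regression of the marker on rejection status, with concurrent infection and post-transplant visit as covariates. Allow for repeated samples per patient, because one recipient can contribute both rejection and stable samples.
3. Report rejection v stable and rejection v infection as named contrasts, alongside rejection v all non-rejection.
4. Name infection as a covariate in the Cox model.

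The cost is revised wording, one derived variable from clinical results already obtained, and slightly more analysis work. The stable and infection contrasts use fewer samples. In the illustration at d = 0.6, dropping 30% of comparators lowers power only from 0.94 to 0.90. No new samples or visits are needed.

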## **35. SUMMARY**

Transplantation saves the lives of patients with end stage lung disease. Better operative techniques, anaesthesia, organ preservation and more potent immunosuppression have improved outcomes significantly but long-term graft survival remains unchanged. Transplanted lungs are lost due to an ill-defined process called chronic lung allograft dysfunction (CLAD) that is characterized by either fibrosis of the airways (bronchiolitis obliterans syndrome = BOS) or of the lung architecture (restrictive allograft syndrome = RAS) (1). CLAD is characterised by a drop in lung function, that once established is irreversible. The major risk factors for CLAD are i) acute rejection as diagnosed on lung biopsy and ii) infection, particularly CMV and aspergillus. To date, biomarkers have not been identified that can diagnose acute rejection or predict the early onset of CLAD.

We have previously explored a number of biomarkers and demonstrated an association with allograft dysfunction following lung transplant (LTx). We have shown that activin and follistatin levels vary with time from LTx and reflect a proinflammatory environment (2,3). We continue to explore the role of NK cells following LTx having previously shown that NK cells become activated in patients undergoing acute rejection or CMV infection (4, 5). Collaborative research with the Doherty Institute has demonstrated a link between immune cells that control CMV and the later development of CLAD (6). We now wish to extend this biomarker approach with a new prospective cohort of LTx patients who will provide blood and BAL samples to allow further interrogation of immune and infectious links to allograft dysfunction following LTx.

Identifying CLAD at an early stage, may allow therapeutic interventions to interrupt the progression to irreversible damage to the transplanted lung. We propose to analyse in both a cross-sectional and longitudinal study whether a series of biomarkers can predict for episodes of acute rejection or the development of CLAD in a cohort of patients undergoing LTx at the Alfred Hospital.

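### The univariate biomarker tests have no time-since-transplant term and no fixed sample time, so a marker of time can be taken for a marker of rejection or CLAD

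*Supplement*

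**What the plan says.** The analysis section of version 4.0 (Section 43) is one paragraph. Its marker comparison reads: "Univariate analysis of the biomarkers and their association with the clinical end-points of acute rejection and CLAD will be performed using the Chi-square test", followed by the t test and the Mann-Whitney test for continuous markers. Confounder adjustment appears only in the next sentence: "Time to acute rejection and CLAD will be analyzed using univariate and multivariate Cox proportional hazards regression, adjusting for potential confounding factors". The threshold is: "A two-sided p-value of 0.05 will be considered to be statistically significant". The section does not give the sample time for each comparison, how several samples from one patient are handled, the Cox time origin, or how serial marker values enter the Cox model.

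Other sections bear on this:

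- Section 35 (Summary) reports earlier work: "We have shown that activin and follistatin levels vary with time from LTx and reflect a proinflammatory environment".
- Section 41, 8.2.1 collects BAL at "surveillance bronchoscopy at 1 day, 2 and 6 weeks and 3, 6, 9, 12 and 18 months post-transplant", and also at bronchoscopies prompted by clinical concern.
- Section 38, 5.3 gives "34% of adult LTx recipients experiencing at least one episode during the first year", calls CLAD a later development, and says BAL findings in rejection must be read against those in stable recipients. It names chronic airway infection as a confounder, but not time.
- Section 37, aim 4.1 describes responses "measured cross-sectionally and longitudinally during the three year post-LTx". Section 43 contains no longitudinal model.

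**The concern.** A two-group test attributes any marker difference to endpoint status. If the two groups of samples were taken at different times after transplant, a change common to all recipients, such as recovery from surgery, shows up as a difference between groups. The plan supplies two of the ingredients itself: at least two markers that move with time, and sampling over 18 months with extra samples when there is clinical concern. Sampling time can therefore depend on the endpoint.

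This is a bias in the estimate. It is separate from the standard-error problem of repeated samples, and it remains if each patient contributes one sample taken at differing times. The study's hypothesis is that markers predict rejection and CLAD. A marker of recovery time could be reported as one of rejection, and a true marker moving against the time trend could be hidden.

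**Working it through.** The plan gives no power, effect size or event target on this point, so there is no figure of its own to reproduce. The check is a simulation of a marker with no relation to rejection.

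**Inputs from the documents.** About 150 patients (Section 42); 34% with rejection in the first year, so 0.34 × 150 = 51; the scheduled visits from 2 weeks to 18 months (seven times, leaving out day 1); two-sided 0.05.

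**Assumptions not in the documents.** Within-patient correlation 0.3. Marker drift of 0, 0.5 or 1.0 SD between 2 weeks and 18 months, linear in log time. Chance of a first rejection at a visit at time t (years) proportional to exp(−kt), with k = 0, 1.5 or 3, scaled to 34% by month 12. Here k = 0 means an equal chance at each scheduled visit. The sample at the rejection visit is compared with all other samples; 600 replicates per scenario.

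**False-positive rate (nominal 5%, simulation error about 1 point).**

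| Drift | k | Pooled t | Pooled Mann-Whitney | With visit terms | Fixed 3-month t | Cox, current value |
|---|---|---|---|---|---|---|
| 0 | 0 to 3 | 3-5% | 4-5% | 5-8% | 4-6% | 5-6% |
| 0.5 SD | 0 | 3% | 3% | 4% | 6% | 4% |
| 0.5 SD | 1.5 | 8% | 7% | 5% | 5% | 5% |
| 0.5 SD | 3 | 19% | 18% | 6% | 6% | 6% |
| 1.0 SD | 0 | 5% | 5% | 6% | 5% | 5% |
| 1.0 SD | 1.5 | 25% | 25% | 6% | 5% | 7% |
| 1.0 SD | 3 | 53% | 51% | 4% | 5% | 3% |

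**Check by hand of the worst row (1.0 SD, k = 3).** Position on the drift curve is f = ln(t/t₁)/ln(t₇/t₁), which gives 0, 0.300, 0.511, 0.700, 0.811, 0.889 and 1 at the seven visits. The mean over all samples is 0.602; weighted by exp(−3t) it is 0.305 for event samples. There are 150 × 7 = 1,050 samples, 51 of them event samples, so

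- mean difference = (0.602 − 0.305)/(1 − 51/1,050) = 0.31 SD;
- marker SD = √(1 + 0.108) = 1.053, where 0.108 is the variance of f over visits;
- SE = 1.053 × √(1/51 + 1/999) = 0.151;
- z = 0.31/0.151 ≈ 2.07, and P(significant) ≈ Φ(2.07 − 1.96) ≈ 0.54, against 0.53 simulated.

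The whole 0.31 SD comes from when the samples were taken.

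**CLAD.** A separate null simulation used 150 × 8 samples with independent errors, an early/late marker shift, half the schedule at or before 3 months, and 20 or 40 CLAD samples assumed all to be late. It gave 9-11% at 0.25 SD, 18-33% at 0.5 SD and 52-82% at 1.0 SD. By hand for 20 events at 0.5 SD: early share of non-event samples 600/1,180 = 0.508; difference 0.5 × 0.508 = 0.254; SE about 0.232; z ≈ 1.09; probability about 0.19, against 18% simulated. An early/late term brought the rate back to 4-6%.

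**Dependence on unstated choices.** With one sample per patient and a flat hazard, comparing the event sample with the controls' 18-month sample gave 17% (0.5 SD) and 44% (1.0 SD). Drawing the control sample from a random visit gave 5-7% for rejection. For 30 assumed CLAD samples at months 9-18, random control visits still gave 11% and 29%.

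**The case against.** The strongest reply is that Section 43 never says samples are pooled over visits or that endpoint status is assigned to each sample. Parts of the plan point the other way: the DSA, NK-cell and microarray work is set at 3 and 12 months, Aim 3 is described by timepoint, and aim 4.1 concerns later rejection and subsequent CLAD, which suggests a comparison of patients. A fixed 3-month test shows no inflation (4-6%). With patient-level status on complete schedules, pooling gave 5.1%, 4.0% and 2.8% at 0.25, 0.5 and 1.0 SD. This stands, except that for-cause bronchoscopies make schedules unequal.

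The timing of rejection is also assumed. The 34% is a first-year incidence and does not show clustering before 3 months. Seven of the eight scheduled visits fall within the first year. If rejections were even over those seven, 4/7 = 57% would be early, against 4/8 = 50% of all samples, and the rate would be 4.7%, 5.9% and 7.3% at 0.25, 0.5 and 1.0 SD. This stands too.

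Third, the same section plans Cox regression. With transplant as origin and the current marker value, it compares patients at equal time and gave 3-7%. That protection depends on choices the plan does not state: with each patient's mean marker up to the event or 18 months entered instead, a null marker gave 15% at 0.5 SD and 49% at 1.0 SD, against 6% with no drift. The univariate tests are in any case planned in their own right.

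Finally, the statement on time variation covers activin and follistatin only, and neither is named in the specific aims. The eplet mismatch score is fixed at transplant and cannot drift. A reader might infer that all the markers drift; the documents do not say so.

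**Conclusion.** The point holds as a gap in specification with a real route to bias. The named univariate tests cannot separate time from endpoint, and the plan does not fix the sample time or the unit to which endpoint status belongs. For rejection, the false-positive rate is roughly 7-19% at 0.5 SD drift and 25-53% at 1.0 SD when event and non-event samples are pooled and rejection clusters early. It stays near 5% when rejection is spread evenly over visits or the test is at a fixed visit. Late CLAD samples are exposed under the same kind of pooling.

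These sizes rest on assumed drift, event timing and CLAD counts. The 150 × 8 layout behind the CLAD rates is also generous: version 4.0 recruits only single-lung recipients from January 2021 (10-15 patients are planned), and version 3.0 took day-1 BAL only in that sub-study.

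A reader might go further and infer that the plan will declare markers of time to be markers of rejection or CLAD. The documents do not support that: it would need pooling, sample-level status, drift and uneven event timing together, and the plan establishes drift for two markers and leaves the rest open. This is a cheap improvement to make before analysis.

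**What to change.** In Section 43, state for each univariate comparison which sample is used and whether endpoint status is per sample or per patient, and make the comparison conditional on time since transplant. Two ways serve:

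- Compare endpoint with non-endpoint samples in the same scheduled visit window, by a van Elteren (stratified Mann-Whitney) test or conditional logistic regression matched on time.
- Model the marker on endpoint status with visit as a categorical term, or a spline in days since transplant, and a patient effect for repeated samples.

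Place for-cause samples at their actual day. For the Cox models, specify transplant as the time origin and enter the marker as a landmark value or as a time-dependent current value.

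This changes wording only. It uses sampling dates that the study will already hold and needs no new samples. The cost is a few degrees of freedom and fewer comparators for for-cause samples that fall far from a scheduled visit.

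### The plan names Student's t test for groups whose sizes are set by event rates; unless the groups are near equal, its 5% error level depends on equal SDs, and Welch's test removes that dependence at little cost

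*Supplement*

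**What the plan says.** The Analysis section of v4.0 (section 43) sets out a univariate step in which each biomarker's "association with the clinical end-points of acute rejection and CLAD will be performed" by one of three tests. These are the chi-square test for proportions, "Student's t test for normally distributed continuous variables", and the "Mann-Whitney U test for non-normally distributed variables". The section mentions neither an unequal-variance form of the t test nor a check of variances. The criterion is "A two-sided p-value of 0.05 will be considered to be statistically significant". Time to rejection and time to CLAD are analysed separately by Cox regression.

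Three other statements bear on the group sizes:

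- Section 42 gives the enrolment: "Approximately 150 patients, including 10-15 single lung transplant recipients, will be enrolled at The Alfred Hospital".
- Background section 5.3 gives the only event rate in the document: "34% of adult LTx recipients experiencing at least one episode during the first year".
- Section 8.3 gives the follow-up: "All participants will be followed for a total of 3 years following lung transplant".

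The document gives no CLAD rate, no three-year rejection rate and no SD for any biomarker.

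**The concern.** Student's t test, named without qualification, is ordinarily the version that pools the two sample variances. Pooling gives the larger group most of the weight in the variance estimate, while the smaller group contributes most to the true sampling error of the difference in means. If the smaller group is the more variable, the standard error is too small and markers are declared too often. If it is the less variable, the standard error is too large and real differences are missed. Equal group sizes largely remove the problem, but the groups here are formed by whether an event occurs, so the plan does not control their sizes.

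Unequal spread is plausible in this setting. Broad Project Aim 4.2 asks whether infection further raises the biomarkers, and Background section 5.3 warns that chronic airway infection confounds the lavage findings seen in rejection. An event group that mixes inflammatory states could therefore be more variable. Nothing in the document establishes this. What is at stake is whether the stated 5% level means 5% in the univariate screen of markers.

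**Working it through.** **Inputs from the document.** Two-sided level 0.05 (section 43); about 150 patients (section 42); 34% with rejection in the first year (section 5.3).

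**Inputs assumed.** The ratio *r* of event-group SD to non-event-group SD, taken as 0.5 to 2; any CLAD split; and any rejection split other than 34%.

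**Group sizes.** 0.34 × 150 = 51 with the event and 150 − 51 = 99 without, a ratio of 1:1.94.

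**Formulas.** Set the non-event SD to 1. On average the pooled test uses

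- pooled variance: s² = [(n₁ − 1)r² + (n₂ − 1)] / (n₁ + n₂ − 2)
- assumed squared standard error: A = s²(1/n₁ + 1/n₂)

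whereas the true squared standard error is B = r²/n₁ + 1/n₂. With no difference in means, the error is approximately 2[1 − Φ(1.96 √(A/B))].

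**The plan's own figure.** With r = 1, A = B and the error is 5.0%. Exact integration over the two sample variances at 51 against 99 also gives 0.0500, which matches the stated level.

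**51 against 99, r = 2.** s² = (50 × 4 + 98)/148 = 2.0135. A = 2.0135 × (1/51 + 1/99) = 0.0598. B = 4/51 + 1/99 = 0.0885. √(A/B) = 0.822, so the error is 2[1 − Φ(1.611)] = 10.7%. Exact integration gives 10.75%, and a simulation of 100,000 datasets gives 10.8%.

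**25 against 125 (assumed), r = 2.** s² = (24 × 4 + 124)/148 = 1.4865. A = 1.4865 × (1/25 + 1/125) = 0.0714. B = 4/25 + 1/125 = 0.168. √(A/B) = 0.652, so the error is about 20%.

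**Type I error of the pooled test at nominal 5%, no difference in means:**

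| Split of 150 | r = 0.5 | r = 1 | r = 1.25 | r = 1.5 | r = 2 |
|---|---|---|---|---|---|
| 51 / 99 (34%) | 1.8% | 5.0% | 6.8% | 8.4% | 10.8% |
| 25 / 125 (assumed) | 0.3% | 5.0% | 9.1% | 13% | 20% |
| 60 / 90 (assumed) | 2.8% | 5.0% | 6.1% | 7.0% | 8.3% |
| 75 / 75 (assumed) | 5.1% | 5.0% | 5.0% | 5.0% | 5.1% |

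**What doubling would need.** At 51 against 99 the error reaches 10% only at r of about 1.82, a variance ratio of about 1.82² = 3.3. At 60 against 90 it needs r of about 3.4. At 75 against 75 it is never reached.

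**Welch's test.** In the first two splits of the table its error stays between 4.9% and 5.1% for these values of r. Its price when the SDs really are equal, by simulation: power 82.0% against 82.2% for the pooled test at 51 against 99 (true difference 0.5 SD), and 75.8% against 77.6% at 25 against 125 (0.6 SD).

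**The case against.** Five points can be made for the plan, and most of them limit the finding.

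- **Unequal variance is not shown.** No biomarker SD appears in the document, and the reverse pattern makes the test conservative. This stands, so every figure above is conditional on *r*. It does not vindicate the pooled test, since a 2% error in a marker search means lost power.
- **The 1:2 split rests on a first-year background rate.** Follow-up is three years, and section 43 does not limit rejection to the first year. Later episodes can only raise the share, which moves the groups towards balance until it passes one half. This also stands. At 60 against 90 the error is 7.0% to 8.3% for ratios 1.5 to 2, and at 75 against 75 it is about 5%.
- **The CLAD split is assumed.** This stands; the 13% to 20% only illustrates what a rarer endpoint would do.
- **Scope is narrow.** Markers judged non-normal go to the Mann-Whitney test, and a marker with much wider spread in event patients may be among them. The Cox models do not use the t test. This stands.
- **Student's t test may be meant loosely,** with the analyst free to use the unequal-variance form. That is possible, but the text does not say so.

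A reader might infer that the error rate doubles or worse whenever the smaller group is more variable. The figures do not support that: at 51 against 99, ratios of 1.25 to 1.5 give 1.4 to 1.7 times the nominal level. A reader might also infer that the design itself makes the variances unequal. Nothing in the document shows that.

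**Conclusion.** The point holds as a conditional weakness with a simple remedy. As written, section 43 ties the 5% level of its t tests to equal SDs in groups that are likely to be unequal in size. If the split is 51 against 99, the actual level is about 7% to 11% when the event group's SD is 1.25 to 2 times larger, and about 2% when it is half as large. A rarer endpoint would widen that range and near-equal groups would close it. The size rests on assumed SD ratios, on carrying a first-year rate over to the whole cohort and, for CLAD, on an assumed share. The choice of Welch's test does not depend on those assumptions: it keeps about 5% in the unequal splits examined and gives up little power when the SDs are equal.

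**What to change.** In section 43, replace Student's t test by Welch's unequal-variance t test for the continuous markers judged normal. The Mann-Whitney tests and the Cox models need no change on this account.

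The cost is one phrase in the protocol. It needs no extra patients or samples. With equal SDs the loss is about 0.2 points of power at 51 against 99 and about 2 points at 25 against 125. Log transformation of all markers is optional and is not needed to cure this defect.
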